### Implementation strategy

The implementation strategy to facilitate the adoption of the recommended intervention in clinical practice was developed in three main steps:First, we analysed the factors or determinants that have played a key role in the feasibility of setting up a primary prevention programme for T2D in the context of a previous clinical trial, the PreDe trial [13]. For this purpose, the health professionals of the participating centres carried out a three-part structured process: (a) individual identification of the main barriers and facilitators in putting the intervention programmes into practice; (b) individual rating of the importance or impact of each factor identified; and (c) pooling and agreed prioritisation of the factors using a nominal group technique, that resulted in a priority list of determinants/targets for improvement of T2D prevention in PHC.In a second step, we designed a tailor-made strategy to address the aforementioned determinants related to clinical practice for T2D prevention, on the basis of theoretical implementation frameworks. For this, each of the determinants identified was framed in one of the possible implementation constructs/determinants and subsequently one or several specific techniques or strategies for overcoming/strengthening the barriers/facilitators in accordance with theoretical frameworks for implementation, the Consolidated Framework for Implementation Research (CFIR), and Theoretical Domains Framework (TDF), and a compendium of implementation strategies [23, 37, 38].Based on previous experience [39–42], the research team involved in the implementation organised and operationalised the specific strategies into actions to be put into practice in the health centres in a framework of a dynamic implementation process.

The same multifaceted implementation strategy will be applied in all the centres, yet the process for establishing the community of practice will differ (Table 1). The first step of the process is the consensus-based selection in each centre of the local leader and his/her subsequent training (15 h over three sessions), organised by comparison group (global or sequential). The first session will have the same content for both groups and will seek to enable the local leaders to acquire the necessary knowledge on primary prevention of T2D and the recommended clinical intervention. The second session will address aspects of the assessment of the organisational and inter-personal structure of the corresponding centre as well as communication and leadership techniques and skills. The third session will be focused on drafting the implementation plan and will address the strategies and procedures to be used in each group. Subsequently, we will provide theoretical and practical training related to the evidence-based clinical intervention for the primary prevention of T2D (90 min) and the computer support tool (6 h). The training will consolidate the differences between the strategies, in that in the sequential group only the nurses will initially receive this training, training for doctors being postponed until after the planning and the carrying out of the cycles of piloting.

**Table 1 Tab1:** Outline of implementation actions by comparison group

**Implementation actions: goals and concrete strategies**	**Comparison Groups (Target agents)**	
**Facilitated community of practice**		
*Goals* *: to facilitate a collaborative learning environment to improve the implementation of clinical innovation.* *Concrete implementation strategies:* *Create a learning collaborative, Facilitation in the form of outreach visits*	**Global** *Intergroup partnership* and *Relationship building*	**Sequential** *Pragmatic cooperation*
**Strengthening of Local Leadership** *Goals* ***:*** *to provide the local coordinator with skills in primary prevention of T2D and interpersonal and organisational strategies to support the implementation.* *Concrete implementation strategies* *: Recruit, designate and train for leadership; Educational meetings.*		
**3 training sessions** (5 hours/session)	Local leaders for global strategy	Local leaders for sequential strategy
**Training in clinical intervention** *Goals* *: to provide initial training in recommended effective clinical intervention for the prevention of T2D and in how to use the information technology support tool in the electronic health record.* *Concrete implementation strategies* *: Educational and capacitation meetings; Changes in record systems*		
**Session 1**: Primary prevention of T2D in PHC: evidence and recommended practice (90 min) **Session 2**: Computer application for the promotion of healthy habits in the Electronic Health Record (6 hours)	Doctors and Nurses	Nurses
**Collaborative structuring of the programme** Goals: to plan the local programme based on shared decision-making concerning: objectives, actions, agents, work flow, organisation and sharing out of tasks. *Concrete implementation strategies**: Local needs assessment; Educational and outreach meetings eliciting local consensus discussion; Ongoing training; Cyclical small tests of change; Develop a formal implementation blueprint*		
**Session 3** – Needs assessment and prioritisation of areas for improvement in T2D prevention (90 min)		
**Session 4/5** – Planning T2D prevention programme (180 min) **Session 6**: Plan-Do-Study-Act cycle 1 (90 min)		Nurses (*Prescription→Screening*)
**Session 7**: Plan-Do-Study-Act cycle 2 (90 min)	Doctors and Nurses (*Screening→Prescription*)	
**Session 8**: Refresher training (180 min)		Doctors and Nurses (*from the 2*^*nd*^ *pilot**)
**Session 9:** Plan-Do-Study-Act cycle 3 (90 min)		
**Session 10**: Final standardisation of the local T2D prevention programme (90 min)		
**Ongoing sustainability** *Goals* *: to continually support and assess innovation being put into practice.* *Concrete implementation strategies* *: Develop quality monitoring systems; Audit and provide Feedback; Ongoing training*		
Regular audits and ongoing facilitation: 6 follow-up sessions over the course of 12 months (90 min X 6 sessions) Continuing education in clinical intervention and information technology tools	All participating professionals	

*A more extensive session lasting 120 min is required to share information about the preliminary programme, suggest pragmatic cooperation and organise the second pilot (2^nd^ PDSA)

Bolded text refers to an implementation action (composed of multiple concrete implementation strategies responding to a implementation goal) or to the work sessions to be held within an implementation action

Underlined text refers to implementation goals or concrete implementation strategies pertaining to an implementation action

Once the training and skill acquisition phase is over, we will start the collaborative modelling process, based on the establishment of a community of practice headed by a local leader and an external facilitator. In the global strategy group, this will be undertaken jointly by participating doctors and nurses from the outset, seeking to adapt the set of clinical activities in a logical way: screening for risk (selecting from among the recommended approaches), gathering of information on individuals’ habits, provision of advice, and intensive intervention with prescription of personalised plans for lifestyle change. In this way, it is hoped that a community of practice will be fostered based on an approach that lies between “Intergroup partnership” and “Relationship building” [26], underlining collaboration between professional categories from the beginning [36]. In the sequential group, first the nurses will consolidate the execution of the clinical intervention at their level, working through from the last “active ingredient” to the first, that is, from the prescription of personal plans to screening. Subsequently, they will involve doctors in the framework of a community of practice underpinned by “Pragmatic cooperation” [26], underlining the independence of each professional category [36].

Once a preliminary programme for primary prevention of T2D has been planned, we will move onto a process of brief pilots of specific actions to assess their efficiency and, thereby, optimise the set of actions of the programme. In the global group, doctors and nurses will collaborate in the piloting process (with joint participation across the professional categories). On the other hand, in the sequential group, once the clinical intervention has been started by nurses, the first cycle of piloting will be undertaken. After this, pragmatic cooperation of doctors will be sought to maximise the efficiency of the actions, flows and procedures of the intervention programme, doctors being involved in the second cycle of piloting. The collaborative process is completed with a further training on the clinical intervention and the IT support tool (this being the initial training of doctors in the sequential group), a third piloting cycle to finalise the details and final standardisation of the programme. The aim of this standardisation is to establish and set the standards for practice, the target population for the intervention and screening strategy, and key components of the intervention and follow-up: broken down by action and process, staff involved, material and organisational components, and factors specific to the context of the centre, among others. The programmes will then be incorporated to the portfolio of services of the centres.

The last element of the strategy is follow-up or sustained support, which will involve six follow-up sessions over 12 months (every month for the first 3 months, then at 6, 9 and 12 months) and the use of auditing reports, presented jointly by the local leader and the external facilitator.

### Assessment of results

Main outcome measures: effectiveness in the optimisation of clinical practice for the primary prevention of T2D (experimental comparison) (see Table 2 for a detailed description):The proportion of professionals who actively adopt the intervention programme, out of the total in each centre (adoption)The proportion of individuals in whom clinical practice recommendations on the screening for T2D risk are met out of the total number of potentially eligible individuals seeking medical care (reach and coverage)The proportion of non-diabetic patients at high risk of developing T2D exposed to interventions related to lifestyle habits 12 months after the introduction of the intervention programmes: assessment of lifestyle habits, provision of personalised advice, prescription of lifestyle changes and follow-up (execution of the recommended clinical intervention).Secondary outcome measures: clinical effectiveness of the intervention (observational comparison)

**Table 2 Tab2:** Main outcome measures

**Effectiveness in the optimisation of clinical practice for the primary prevention of T2D (experimental comparison)**	
**Measures**	**Timing and Source**
**Coverage**: Screening indicators (depending on the screening strategy selected by the centre)	
*Case 1* *: T2D screening as part of opportunistic screening for cardiovascular risk in individuals aged ≥45 years or ≥30 years with at least one known risk factor:* • % of non-diabetic patients aged ≥30 years with a cardiovascular risk factor (e.g., hypertension or BMI ≥30 kg/m2 or hyperglycaemia) attending to family doctor office in whom clinical practice guidelines are followed in terms of T2D screening using fasting glucose levels in the previous year; • % of non-diabetic patients aged ≥45 years with no cardiovascular risk factor attending to family doctor office in whom clinical practice guidelines are followed in terms of T2D screening using fasting glucose levels in the previous 4 years.	
*Case 2* *: T2D screening based on a BMI≥25 kg/m2 in individuals aged 40 to 70 years:* • % of non-diabetic patients aged between 40 and 70 years attending to family doctor’s office whose BMI has been measured in the previous year, 12 months after the introduction of the T2D prevention programme in the centres;	Baseline and 12 months after the setting up of the programme
• % of non-diabetic patients aged between 40 and 70 years attending to family doctor’s office with a BMI≥25 kg/m2 who have been screened for T2D using fasting glucose in the previous year, 12 months after the introduction of the T2D prevention programme in the centres.	Electronical Health Record
**Implementation**: Execution of the elements of the intervention programme in high risk patients defined by the presence of prediabetes (fasting glucose 110-125 mg/dl)	
•% of patients whose physical activity levels and diet have been assessed, after the identification of T2D risk; •% of patients who have been given preventative advice concerning the need to increase physical activity and eat a healthy diet, after the identification of T2D risk;	
•% of patients who have been prescribed a plan for increasing physical activity and eating a healthy diet, after the identification of T2D risk;	Baseline and 12 months after the setting up of the programme
•% of high risk patients (fasting glucose 110-125 mg/dl) who have undergone annual testing of fasting glucose and HbA1c.	Electronical Health Record
**Maintenance:** Long-term execution of the healthy lifestyles promotion programme in T2D high risk patients	
•Level of screening coverage among candidate patients (e.g., % of patients with screening for T2D) •Level of execution of the clinical intervention elements (e.g., % of pre-diabetic patients who have received a prescription for lifestyle change) 24 months the introduction of the programme	0 to 24 months after the setting up of the programme (monthly rate)
•Monthly rate of the change in the coverage and execution of intervention elements for the promotion of healthy lifestyles over a 24-month period.	Electronical Health Record
**Spreading:** healthy lifestyles promotion actions in attending patients who do not meet the criteria of high risk of T2D (e.g., overweight or obese patients with normal glucose levels).	
•% of patients whose physical activity levels and diet have been assessed, from those attending aged 10 to 80 years;	
•% of patients who have been given preventative advice concerning the need to increase physical activity and eat a healthy diet, from those attending aged 10 to 80 years;	Baseline, 12 and 24 months after the setting up of the programme
•% of patients who have been prescribed a plan for increasing physical activity and eating a healthy diet, from those attending aged 10 to 80 years;	Electronical Health Record

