**Methods:**

This will be a randomised cluster type II hybrid implementation trial. Nine PHC centres from the Basque Health Service (Osakidetza) will be allocated to two different procedures to engage family doctors and nurses and create an interprofessional collaborative practice to optimise the integration of a T2D primary prevention programme. All centres and PHC professionals will receive training on current guidelines in primary prevention of T2D and effective interventions to promote healthy lifestyles. Headed by a local leader and an external facilitator, centres will conduct a collaborative structured process to model and adapt the intervention and its implementation to the specific context of professionals and centres. One of the groups will apply this strategy globally, promoting the cooperation of all health professionals from the beginning. The other will perform it sequentially, centred first on nurses, who will then seek the pragmatic cooperation of doctors. All patients without diabetes aged ≥ 30 years old who attend collaborating centres at least once during the study period and found to be at high risk of developing T2D will be eligible for programme inclusion. The main outcome measures focus on changes observed in indicators of T2D prevention clinical practice at centre level after 12 and 24 months, associated with the application of one or other engagement procedure. Secondary outcomes will compare their clinical effectiveness in changing eligible exposed patients’ main lifestyle behaviours and risk factors (physical activity and diet, weight, etc.) after 12 months.

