#### Users of primary care services

All the patients aged between 45 and 70 years old who seek medical attention in the participating centres at least once with a high risk of developing T2D and/or with moderate hyperglycaemia (high baseline glucose levels or glucose intolerance), but no diagnosis of T2D documented the medical record, will be candidates to participate in the T2D prevention programme.

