### Recommended clinical intervention based on evidence and clinical practice guidelines

Based on the available scientific evidence and clinical practice guidelines [2, 4, 13], three measures are recommended for the prevention of T2D in clinical settings:

(1) Screen for individuals with abnormal regulation of glucose or a high risk of developing T2D (fasting glucose ≥ 110–125 mg/dl, HbA1c ≥ 6%), with the following approaches being recommended: T2D screening as part of opportunistic screening for cardiovascular risk in individuals ≥ 45 years old or ≥ 30 years old with at least one known risk factor (e.g. hypertension); T2D screening based on a body mass index (BMI) ≥ 25 kg/m^2^ in individuals between 40 and 70 years old; or screening for T2D risk using the FINDRISC [13] scale in individuals between 45 and 70 years old. These last two procedures should be completed with a fasting glucose to discard T2D diagnosis.

(2) In patients identified as high risk, carry out a structured intensive programme focused on the prescription of personalised plans for lifestyle change (low-calorie and low-fat diets, and at least 150 min of exercise per week). This intensive intervention requires the assessment of lifestyle habits, personalised advice (tailored to the individual’s risk) and the setting of objectives and plans or prescription of a personalised intervention for lifestyle change. It should combine education with the use of theoretically-grounded evidence-based strategies for behavioural change and the introduction of changes in daily life.

(3) Ensure that the intervention is followed up to keep participants motivated, with frequent contact at the beginning and subsequently annual follow-up.

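### Coverage, a main outcome, takes its indicator from the screening route each centre picks after randomisation, and no common between-arm measure is fixed

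*Protocol article*

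**What the plan says.** Assessment of results lists coverage among the main outcomes of the randomised comparison and describes it generically: "The proportion of individuals in whom clinical practice recommendations on the screening for T2D risk are met out of the total number of potentially eligible", the denominator being people who seek care. Table 2 then makes the indicator conditional: "Screening indicators (depending on the screening strategy selected by the centre".

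Two cases follow in Table 2, both read from the electronic health record at baseline and 12 months:

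- **Case 1, opportunistic cardiovascular screening.** Fasting glucose in the previous year among attenders aged 30 or over with a risk factor. For attenders aged 45 or over without one, compliance is judged "in terms of T2D screening using fasting glucose levels in the previous 4 years".
- **Case 2, BMI route.** BMI measured in the previous year at age 40 to 70, and fasting glucose in the previous year among those aged 40 to 70 with BMI of 25 or more.

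The section on the recommended clinical intervention permits three routes: "T2D screening as part of opportunistic screening for cardiovascular risk in individuals ≥ 45 years old or ≥ 30 years old with at least one" recognised factor, BMI at age 40 to 70, and the FINDRISC "scale in individuals between 45 and 70 years old". Table 2 has no case for the third.

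On timing, Random allocation says the sequence is obtained before the trial starts. Implementation strategy places the choice of route within the collaborative modelling process, described for the global arm as "screening for risk (selecting from among the recommended approaches" and then the later steps. The screening strategy and target population are set at final standardisation, after the third pilot cycle.

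**The concern.** A randomised comparison needs an outcome defined in the same way in both arms. Here the numerator, denominator and look-back follow a decision taken after allocation, as part of the strategy under test. Randomisation does not protect a comparison from differences that arise in this way.

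The choice could plausibly differ by arm. In the global arm, doctors and nurses work together from screening towards prescription. In the sequential arm, nurses begin alone and work from prescription back to screening, and doctors join at the second pilot. Different people reach the decision in a different order.

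If the mix of routes differs, the estimated effect on coverage combines the effect of the engagement procedure with the effect of which indicators were counted. The Analysis section puts the emphasis on the magnitude of differences rather than on significance, so an artefact in magnitude matters directly.

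**Working it through.** The article states no coverage figure, so there is none to reproduce. The check has three steps.

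**1. Routes against indicators.**

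| Permitted route | Denominator in Table 2 | Numerator | Look-back |
|---|---|---|---|
| Cardiovascular risk (Case 1) | age ≥30 with a risk factor | fasting glucose | 1 year |
| | age ≥45 without a risk factor | fasting glucose | 4 years |
| BMI (Case 2) | age 40–70 | BMI measured | 1 year |
| | age 40–70 with BMI ≥25 | fasting glucose | 1 year |
| FINDRISC, age 45–70 | none | none | none |

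Three routes are permitted and two have indicators, four indicators in all. The article states no rule for combining them across centres and no indicator common to all centres.

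**2. Can the mix balance?** Let s be the number of Case 1 centres among the five sequential centres and t the number among the four global centres. The mix is equal when s/5 = t/4, that is 4s = 5t. With s from 0 to 5 and t from 0 to 4, the only solutions are (0, 0) and (5, 4): all nine centres on the same route. Once both routes are in use, the mix is unequal.

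**3. Size of the artefact.** Let g be the gap between the Case 1 and Case 2 indicators when practice is identical. Weighting centres equally,

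spurious arm difference = g × (s/5 − t/4).

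The gap g is an assumption, because the documents give no value. I take 5 to 30 points.

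| Case 1 centres, sequential v global | s/5 − t/4 | Spurious difference (points) |
|---|---|---|
| 3/5 v 2/4 | 0.10 | 0.5 to 3.0 |
| 4/5 v 2/4 | 0.30 | 1.5 to 9.0 |
| 4/5 v 1/4 | 0.55 | 2.8 to 16.5 |
| 5/5 v 0/4 | 1.00 | 5 to 30 |

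For scale, Sample size plans on 65% v 50%, a difference of 15 points. At g = 20, a split of 5/5 v 1/4 alone gives 20 × (1 − 0.25) = 15 points. That is an extreme split, and the 15 points were used to power the exposure and execution indicators, so they serve only as a yardstick.

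The same formula applies to pre-post differences if g is read as the gap in change from baseline rather than in level. That gap may well be smaller, but nothing makes it zero.

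**The case against.** The strongest reply has four parts.

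- **Local adaptation is intended.** The article treats fitting the programme to each centre as part of the strategy. This stands as a reason to let centres choose their route. It is not a reason to let the outcome definition follow the choice.
- **The planned analysis uses pre-post differences within centres.** These remove part of a level gap between indicators. They do not remove differences in denominator, or in how far each indicator moves for the same improvement in practice.
- **Centres may all choose the same route.** True. The problem arises only if they differ, and nothing in the article ensures that they will not.
- **Pooling rules belong in an analysis plan.** Often so, but here Table 2 itself ties the indicator to the choice. That is a statement in the protocol and not an omission.

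Some stronger readings are tempting, and the documents do not support them:

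- A reader might infer that every centre has its own indicator, or that the arms cannot be compared. There are two indicator sets for nine centres. All inputs come from the electronic record, and Assessment of results gives a generic definition that could anchor a common measure.
- A reader might contrast the 1-year and 4-year look-backs. With one test per three years on a Poisson assumption, coverage would be 1 − exp(−1/3) = 28% and 1 − exp(−4/3) = 74%, about 45 points apart. But both look-backs belong to Case 1 and apply to different patients, and a Case 1 centre reports both. The gap is therefore not a measure of bias between arms.
- A reader might say a FINDRISC centre is lost to the outcome. The article gives that route no indicator, but the route ends in a fasting glucose and the Table 2 indicators can be computed there too.
- A reader might say Case 1 counts patients whom the Methods exclude. The age range in Users of primary care services concerns candidates for the programme, whereas Case 1 follows the screening population of the recommended intervention.

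**Conclusion.** The concern holds in this form: coverage is a main randomised outcome, its indicator depends on a choice made after allocation within the strategy being compared, one permitted route has no indicator, and no common between-arm measure is fixed. If routes differ between centres, the arm difference in coverage is open to an artefact of indicator mix.

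The size cannot be derived from the documents. It ranges from under one point to well above ten, depending on the split of routes and on the assumed gap of 5 to 30 points, with equal centre weights. It is zero if all nine centres choose the same route.

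The screening part of the maintenance outcome in Table 2 may inherit the problem. The execution indicators use one definition for all centres and are not affected.

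There is a separate inconsistency. The abstract gives the programme population as patients without diabetes aged 30 or over "who attend collaborating centres at least once during the study period and found to be at high risk of developing T2D", while Users of primary care services has "All the patients aged between 45 and 70 years old who seek medical attention in the participating centres at least once". The two must be reconciled.

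**What to change.** Compute the Case 1 and Case 2 coverage indicators of Table 2 from the electronic record at baseline and 12 months in all nine centres, whatever route each adopts, including any FINDRISC centre.

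Before centres choose their route, name one of these as the common between-arm coverage measure. Two candidates already in Table 2 are fasting glucose in the previous year among attending non-diabetic patients aged 40–70 with BMI ≥25, or the same test among those aged ≥30 with a cardiovascular risk factor. Report the indicator for the centre's own route as a within-centre description, and apply the same rule to the screening part of maintenance. Separately, make the programme age range in the abstract and the Methods agree.

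The cost is a few extra queries on records already being extracted, and revised wording in Table 2. The downside is small: the common measure may not match the route a centre adopted, so each centre's route should be reported beside it.
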